##### Duration of study

The overall duration of the trial is expected to be approximately 36 months. Recruitment of the patients is planned over a time period of 12 months, and the duration of follow-up per patient (start at treatment initiation) will be 24 months (Fig. 1).

**Fig. 1 Fig1:**
[figure not shown]
Study flow chart

#### Standard case management

##### Relapse management

Relapses will be treated by reinstitution of daily therapy with prednisolone (2 mg/kg/day, maximum 60 mg) until remission, followed by alternate-day dosing (1.5 mg/kg, maximum 40 mg) for 4 weeks, and then stopped.

##### Other co-interventions

Rituximab will be administered after proper premedications (administer 30 min prior to rituximab) with oral paracetamol, oral diphenhydramine and intravenous hydrocortisone as per center practice.

Hypertension, defined as blood pressure > 95th percentile (for age, height and sex) in those previously normotensive, shall be treated at the discretion of the investigator. Children shall be treated with oral calcium+vitamin D when on oral prednisolone. Other medications shall be used at the discretion of the treating physician. Trimethoprim-sulfamethoxazole shall be administered from the beginning of rituximab treatment until recovery of peripheral blood B cell for prophylaxis against *Pneumocystis jirovecii* infection. The investigator will record all concomitant medications taken by the subject during the study from the date of informed consent, in the appropriate section of the case report form.

#### Safety data

We will collect any untoward medical occurrence in the form of signs, symptoms, abnormal laboratory findings, or diseases that emerges or worsens relative to baseline (i.e. present at the initial study visit). All adverse events including any transfusion reaction following rituximab infusion will be graded according to the Common Terminology Criteria for Adverse Events, version 3 [15]. Policy and approach to define adverse events is reported in Additional file 1: Appendix 2.

#### Study termination

Subjects will be informed that they have the right to withdraw from the study at any time, without prejudice to their medical care, and that they are not obliged to state their reasons. The time and reason of treatment discontinuation will be documented in the CRF. Independent data-safety and monitoring board (DSMB) (or IRB) will monitor the study progress at regular interval.

#### Data management & quality assurance

The investigators will record study data in the case report form (CRF). The clinical and laboratory data shall be entered in electronic format. At monthly intervals, the data entries will be checked for completeness and the files reviewed for errors.

At the end of the study, the data will be transformed into different data formats for archiving and to ensure that it can be reused. It is planned to make the trial data on which scientific publications are based, as well as all the primary data, publicly available in an appropriate online data repository to allow re- and meta-analyses after completion of the trial.

### Study endpoints, estimand definition, power calculation and type of statistical analysis used

#### Study endpoints

##### Primary endpoint

The primary endpoint is the time from treatment initiation to first relapse or death (whichever occurs first).

##### Secondary endpoints

Main secondary endpoint is 1.) the cumulative prednisolone requirement (mg/kg/yr) over the first 12 and 24 months, respectively. Further secondary endpoints are 2.) at least one relapse within the first 12 months (yes/no); 3.) at least one relapse within 24 months (yes/no); 4.) occurrence of two or more than two relapses in any period of 6 months within 24 months (yes/no); 5.) occurrence of four or more relapses in a period of any 12 months within 24 months (yes/no); 6.) at least One episode of life threatening infection or severe relapse (anasarca with hypovolemia or thrombosis) requiring hospital admission within any 12 months (within 24 months) and 24 months (yes/no), respectively; 7.) impairment of renal function (eGFR < 30 ml/min per 1.73 m^2^ or loss of eGFR by > = 30% with regard to baseline) within any 12 months (within 24 months) and 24 months (yes/no), respectively; 8.) t*reatment failure* (yes/no): defined as composite endpoint consisting of the three endpoints as defined above under 5., 6. and 7. referring to month 24; 9.) number and severity of adverse events; 10.) eGFR at 4, 8, 12, 18 and 24 months, respectively; absolute change in eGFR from baseline to 4, 8, 12, 16 and 24 months, respectively; 11.) number of relapses within months 0–24, 0–12 and 12–24, respectively; 12.) number of different steroid toxicity events (new onset) within months 0–24; 13.) off steroids at month 24 (yes/no); 14.) abnormal values in biochemical tests and haematology assessments (yes/no) according to the Common Terminology Criteria for Adverse Events, version 3 [15]; 15.) height SDS at 12 and 24 months, respectively; 16.) absolute change in height SDS from baseline to 24 months; 17.) BMI SDS at 12 and 24 months, respectively; 18.) absolute change in BMI SDS from baseline to 24 months; 19.) total B Lymphocyte count (% and per mm^3^) over time.

#### Estimands

An estimand is defined through the treatment, the targeted population, the variable, a specification of how to handle intercurrent events (postrandomization events) and a population-level summary [16]. In the following, the primary estimand corresponding to the primary objective, as well as the main secondary estimands corresponding to the main secondary objective are described.

##### Primary Estimand

The treatment is described as above and the targeted population is defined through the in- and exclusion criteria who received at least one dose of study treatment. The intercurrent events are handled as follows. Administrative censoring at the end of study, withdrawing and loss to follow-up without prior deterioration are assumed to be uninformative and will be censored. This implies the assumption that censored patients would have behaved as the uncensored patients. Hence, this describes a scenario in which the intercurrent event would not occur (hypothetical strategy). It is assumed that the event death is worse than a first relapse, therefore it is included in the definition of the variable (composite strategy). Deviations from the treatment protocol and treatment switching will be ignored (treatment policy strategy). The population-level summary measure is the hazard ratio.

##### Main secondary Estimands

Treatment and population are specified as for the primary estimand. The variable is defined as the amount of cumulative prednisolone requirement (mg/kg/year) over 12 and 24 months, respectively. Intercurrent events are handled as follows. Withdrawals, lost to follow-up, death, treatment switching, deviations from the treatment protocol and AEs will be ignored (treatment policy strategy). The summary measure is the difference in variable means.

#### Sample size/ power calculation

The sample size calculation is based on the primary endpoint, time to first relapse or death (whichever occurs first), using log-rank test to compare the event times of arm A and B. An event rate of 25% after 24 months in arm A and 5% in arm B was assumed (hazard ratio = 0.178) [12–14, 17–22]. Assuming an individual follow-up time of 24 months, in total 95 patients (15 events) are required to prove efficacy with a power of 90% and a two-sided alpha level of 5% for the log-rank test. To account for major protocol violations and drop-outs an assumed drop-out rate of 10% yields a total of 100 patients to be randomized [23, 24].

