#### Comparisons, randomization & blinding

Treatment arm A will be compared to treatment arm B. Randomization will be performed 1:1 using stratified block randomization with varying block sizes and including age (≤ 7 vs. > 7 years) and renal histology (MCD vs. FSGS) as stratification factors. To achieve comparable intervention groups and to minimize a potential selection bias, patients will be allocated in a concealed fashion by means of randomization after enrolment. To that end, a computer generated random list will be created according to the stratification factors and block sizes and sealed opaque envelopes will be provided by an independent data manager from the Institute of Medical Biometry and Informatics, University of Heidelberg. Enrolment and assignment of the participants to interventions will be done by investigators and resident doctors at NRS Medical College & Hospital, Kolkata, India. The trial will be open-label with no masking of patients or study staff to the treatment allocation.

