MMF maintenance treatment following Rituximab re-exposure in post-Rituximab relapsers also extended the duration of remission, with two thirds of patients remaining relapse-free for 2 years [12]. The long term follow up of our RITURNS trial also revealed better relapse free survival with maintenance MMF therapy following rituximab induction, with a relatively benign side effect profile [14]. A recent retrospective multicenter study revealed that children receiving low-dose rituximab without maintenance immunosuppression had the shortest relapse-free survival, and both the cumulative rituximab dose and maintenance immunosuppression had important effects on treatment outcomes [29].

These observations and considerations motivated us to design a trial comparing these alternative treatment approaches.

RITURNS II will be the first randomised clinical trial comparing the effects of extended B cell depletion by repeated rituximab administration to that of maintenance MMF after a single course of Rituximab in maintaining extended disease remission in children with SDNS. The sample size and evaluation period will be sufficient to empower the assessment not only of differences in therapeutic efficacy but also to obtain valid safety information. The lack of the long term safety data is the main current concern of clinicians precluding extensive use of Rituximab in children with SDNS.

Another strength of this trial will be the exploration of potential markers and mediators of treatment efficacy and adverse effects. We will regularly monitor B-lymphocyte counts, as well as oral drug adherence using patient diaries and returned pill counting.

Potential limitations of our study are given by its single-centre nature, and the lack of blinding which would have required additional administration of placebo tablets and infusions, a procedure that was not deemed acceptable in this vulnerable population of children, nor required given the fact that urine protein measurement is an objective endpoint that is hardly affected by investigator expectation bias. Bias from potential confounding factors will be minimized addressed by inclusion as covariates into the statistical analysis.

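### The stated 90% power is not delivered: under the protocol's own assumptions the log-rank test on 95 patients has about 82% power

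*Protocol article*

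**What the plan says.** The section on sample size and power bases the calculation on the primary endpoint, time to first relapse or death, compared by a log-rank test. The effect assumption is: "An event rate of 25% after 24 months in arm A and 5% in arm B was assumed (hazard ratio = 0.178"). Every patient is taken to be observed for the same period: "Assuming an individual follow-up time of 24 months". The conclusion drawn is that "in total 95 patients (15 events) are required to prove efficacy with a power of 90% and a two-sided alpha level of 5"%. The number to randomise is then set at 100, citing 10% drop-out. The section names no formula and mentions no check by simulation.

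The section on randomisation gives the allocation: "Randomization will be performed 1:1 using stratified block randomization with varying block sizes". The section on statistical analysis makes the confirmatory test a two-sided log-rank test stratified by age group and histology. The Discussion presents the sample size as adequate: "The sample size and evaluation period will be sufficient to empower the assessment not only of differences in therapeutic efficacy".

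**The concern.** The assumed hazard ratio is extreme and the expected number of events is about 14. The usual closed-form sample-size formula for the log-rank test is a large-sample result for effects close to the null. It replaces the true mean of the statistic by one proportional to the log hazard ratio, and it keeps the null variance. Neither simplification is safe at 0.178.

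If the formula is optimistic here, the protocol credits the trial with a power it does not have. The real type II error would be nearly twice the stated 10%. Readers of a non-significant result would take it as stronger evidence against superiority than it is.

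**Working it through.** **Inputs.** From the sample size section: 24-month event rates of 25% and 5%, two-sided alpha 5%, target power 90%, 24 months of follow-up for all, 95 patients, 15 events, 100 randomised, 10% drop-out. From the randomisation section: 1:1 allocation.

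**Step 1: reproduce the protocol's figures.**
- Hazard ratio: ln(0.95)/ln(0.75) = 0.1783, as stated. Its log is −1.724.
- Schoenfeld events: 4 × (1.960 + 1.282)² / 1.724² = 14.14, rounded up to 15.
- Mean event probability: (0.25 + 0.05)/2 = 0.15. Patients: 14.14/0.15 = 94.2, so 95.

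Both figures reproduce, so there is no slip in the arithmetic. With 95 patients the expected number of events is 95 × 0.15 = 14.25.

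**Step 2: see where the approximation fails.** Take 14.25 events and evenly split risk sets.
- Schoenfeld takes the mean of the standardised statistic as ½ × √14.25 × 1.724 = 3.25, with SD 1. Power = Φ(3.25 − 1.96) = 90%.
- The actual probability that an event falls in arm B is 0.1783/1.1783 = 0.151, so the true mean is (0.5 − 0.151) × √14.25 / 0.5 = 2.63, well below 3.25.
- The SD is also smaller than 1: √(0.151 × 0.849)/0.5 = 0.717.
- With both corrected, power = Φ((2.63 − 1.96)/0.717) = Φ(0.94) = 83%.
- Freedman's formula uses the mean of 2.63 but keeps SD 1: Φ(2.63 − 1.96) = 75%. It would ask for 21.6 events (144 patients) for 90%, so it errs on the pessimistic side.

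Step 2 is only a guide, because it fixes the event count and ignores the drift in the risk sets.

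**Step 3: simulate the test itself.** Exponential event times with 25% and 5% at 24 months, censoring at 24 months, 1:1 allocation, two-sided 5% unstratified log-rank test, 30,000 to 40,000 runs per row:

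| Patients | Drop-out | Mean events | Power |
|---|---|---|---|
| 90 | none | 13.5 | 80.3% |
| 95 (47/48 or 48/47) | none | 14.2–14.4 | 82.2–82.4% |
| 100 | none | 15.0 | 84.0% |
| 100 | 10%, exponential | 14.3 | 82.3% |
| 110 | none | 16.5 | 87.7% |
| 116 | none | 17.4 | 89.0% |
| 120 | none | 18.0 | 90.3% |

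Separate runs of 10,000 to 20,000 replicates gave 81.7–82.6% at 95 patients, 84.3–84.9% at 100 without drop-out, 81.9–82.6% at 100 with drop-out, and 79.9–80.5% at 90. The Monte Carlo standard error is at most about 0.4 points, and the gap to 90% is about 8 points.

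**Step 4: the stratified test.** The protocol gives no stratum shares, so they must be assumed. With four strata of 40/10/40/10%, power at 95 patients was 80.2–81.3% across runs. At 100 patients with 10% drop-out it was 80.4–82.0% with those shares and 81.4–81.8% with four equal strata. The overall range is about 80 to 82%.

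**The case against.** The best defence is that nothing was miscalculated. Schoenfeld's formula is a standard method for the test named, the hazard ratio and both counts reproduce, and power of about 82% still clears the customary 80%. Type I error, test, estimand and analysis set are untouched. The hazard ratio is the planned summary measure and the Kaplan–Meier curves will carry confidence intervals, so interpretation need not lean on planned power.

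Much of this stands:
- The fault is an inaccurate approximation, not a slip. Because the section names no formula, one can say only that its figures are consistent with Schoenfeld.
- Freedman's 75% should not be used to size the shortfall, since it misses the simulated value by about 7 points in the other direction.
- About 82% does not by itself contradict the Discussion's claim of sufficiency.
- Stratified power depends on unstated shares and must be given as a range.

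None of it rescues the number. The protocol states the power of a specified test under specified assumptions, and that power is about 82%. Randomising 100 rather than 95 does not help: even with no drop-out it reaches only 84 to 85%.

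**Conclusion.** The concern holds. Under the protocol's own inputs the two-sided 5% log-rank test on 95 patients has about 82% power, about 8 percentage points below the stated 90%. The type II error is about 18% rather than 10%. With 100 randomised and 10% drop-out the unstratified figure is again about 82%, and the planned stratified test lies at about 80 to 82%. Reaching 90% would need about 120 evaluable patients, or about 18 events.

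The result assumes proportional hazards and, for the main figure, common 24-month follow-up. Under those two conditions the log-rank test depends only on the ranks of the event times, so the exponential form is not essential. The drop-out figure also assumes exponential, non-informative drop-out. The stratified range rests on assumed stratum shares.

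**What to change.** In the sample size section, replace the 90% with the simulated power of the planned stratified log-rank test, and say that it was obtained by simulation. For example: with 100 randomised and 10% drop-out, power is about 82%, or 80 to 82% depending on the stratum shares assumed; if only 90 patients contribute, the unstratified test has about 80%. List the assumptions used, including the stratum shares, and carry the same statement into the statistical analysis plan, which is to be finalised before database closure.

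Keep the sample size. Seventy patients had been enrolled by 15 September 2020, and the correction concerns what is claimed for the design, not its conduct. The cost is one sentence in each document and a less favourable figure, with no extra patients.

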#### Statistical analysis

The analysis will be performed on the full analysis set (FAS; according to the intention to treat principle), the per-protocol set and the safety analysis set (for details refer to Additional file 1: Appendix 3).

All documented variables will be analyzed descriptively by tabulation of empirical distribution measures accordingly to the scale level and under specification of the number of non-missing values.

The confirmatory primary analysis will be based on the FAS. The primary endpoint will be compared between the two treatment groups using a two-tailed logrank test stratified by age (≤ 7 vs. > 7 years) and renal histology (MCD vs. FSGS) at an overall type I error rate of 0.05. The survival curves will be estimated using the Kaplan-Meier product-limit method, and the corresponding confidence intervals will be calculated using Greenwood’s formula [25]. Missing values on the covariates will be imputed by a multivariate imputation model. To assess the impact of major protocol deviations, an analogous analysis of the primary endpoint will be performed on the per protocol set. In addition, the possible influence of age (continuous) and renal histology on the primary endpoint is evaluated within a multivariate Cox regression analysis including treatment group (under the assumption of proportional hazards) performed on the FAS. Furthermore, a multivariate Cox regression analysis with covariates, age (continuous), sex, renal histology (MCD vs. FSGS), duration of the nephrotic syndrome (years), number of relapses in previous year and group will be performed on the FAS. All secondary endpoints will be analyzed based on the FAS and the results will be interpreted descriptively.

The **s**afety analysis will be based on the safety analysis set and includes calculation and comparison of frequencies and rates of adverse and serious adverse events reported in the two treatment groups. Furthermore, the relation of AEs with the cumulative dose of Rituximab, MMF and Prednisolone will be described, respectively.

More details can be found in the statistical analysis plan which will be finalized prior to database closure and before performing any analyses. All analyses will employ SAS Version 9.4 or higher.

## Discussion

Existing clinical practice guidelines recommend calcineurin inhibitors (CNI) as first-line steroid sparing therapy for children with SDNS, whereas Rituximab is used as a rescue for CNI resistant cases [7–11]. However, the excellent efficacy and safety profile of Rituximab raised the question whether it could be used as a first-line alternative to CNI therapy. In the RITURNS trial we demonstrated a significant and clinically relevant reduction of relapse rates by primary use of Rituximab as compared to standard CNI therapy during a 12-month observation period, accompanied by a more favourable side effect profile [7]. To further assess the long-term efficacy and safety of the treatment protocols we extended the follow-up of the RITURNS trial cohorts by another 2 years [14]. In this follow-up study we noted disease recurrence in all patients of the Rituximab arm, with first relapses occurring between 6 and 24 months following Rituximab exposure. This finding supports existing literature on rituximab in children with nephrotic syndrome [26–28].

The transient nature of the therapeutic effect of Rituximab creates a need to develop safe and efficient longer-term treatment protocols for SDNS. Repeated prophylactic Rituximab administration is one therapeutic option. Alternatively, an oral maintenance steroid-sparing immunosuppressant can be initiated before B cells are repleted. Encouraging results have been reported for both approaches in retrospective case collections and small cohort studies [12–14, 17–22].

Rituximab re-treatment without any maintenance immunosuppression prolonged the relapse-free survival in previously relapsing patients [19–22]. In the RITURNS trial we demonstrated that B cell counts recovered by 12, 39 and 93% at 6 mo, 9 mo and 12 mo respectively following a single course of rituximab and all relapses occurred beyond 8 months after administration in patients who had achieved full B-cell recovery [7]. Two other trials demonstrated a similar pattern of B-cell depletion following rituximab [26–28]. We chose an 8-monthly re-treatment schedule as a compromise to avoid unnecessary and costly over-immunosuppression on the one hand and extended periods of fully recovered B cell activity at risk of relapses on the other hand.

MMF maintenance treatment following Rituximab re-exposure in post-Rituximab relapsers also extended the duration of remission, with two thirds of patients remaining relapse-free for 2 years [12]. The long term follow up of our RITURNS trial also revealed better relapse free survival with maintenance MMF therapy following rituximab induction, with a relatively benign side effect profile [14]. A recent retrospective multicenter study revealed that children receiving low-dose rituximab without maintenance immunosuppression had the shortest relapse-free survival, and both the cumulative rituximab dose and maintenance immunosuppression had important effects on treatment outcomes [29].

These observations and considerations motivated us to design a trial comparing these alternative treatment approaches.

RITURNS II will be the first randomised clinical trial comparing the effects of extended B cell depletion by repeated rituximab administration to that of maintenance MMF after a single course of Rituximab in maintaining extended disease remission in children with SDNS. The sample size and evaluation period will be sufficient to empower the assessment not only of differences in therapeutic efficacy but also to obtain valid safety information. The lack of the long term safety data is the main current concern of clinicians precluding extensive use of Rituximab in children with SDNS.

Another strength of this trial will be the exploration of potential markers and mediators of treatment efficacy and adverse effects. We will regularly monitor B-lymphocyte counts, as well as oral drug adherence using patient diaries and returned pill counting.

Potential limitations of our study are given by its single-centre nature, and the lack of blinding which would have required additional administration of placebo tablets and infusions, a procedure that was not deemed acceptable in this vulnerable population of children, nor required given the fact that urine protein measurement is an objective endpoint that is hardly affected by investigator expectation bias. Bias from potential confounding factors will be minimized addressed by inclusion as covariates into the statistical analysis.

In conclusion, we perform this randomized clinical trial to compare efficacy and safety of repeated courses of rituximab to that of maintenance mycophenolate mofetil following a single course of rituximab in maintaining remission over 24 months among children with SDNS, to provide an evidence base for the long-term management of children suffering from complicated nephrotic syndrome.

